### Inclusion criteria

Inclusion criteria are as follows: (1) inpatients aged 18–60 years with MDD diagnosed by Diagnostic and Statistical Manual of Mental Disorders, Fifth Edition, Text Revision (DSM-5-TR); (2) comorbid insomnia (PSQI >5, HAMD-17 20–35); (3) no hypnotic or acupuncture treatment in the past month; (4) no cognitive or communication disorders; (5) willingness to provide written informed consent and accept randomization; and (6) patients on a stable dose of antidepressants (e.g., escitalopram, venlafaxine, or mirtazapine) for ≥2 weeks prior to enrolment, and agreeing to maintain the same dosage during the trial, will be eligible (33).

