### Randomization, allocation concealment and blinding

Stratified permuted block randomization will be applied to assign participants to the LA, SLA, and control groups in a 1:1:1 ratio. Stratification will be based on age (18–40 vs. 41–60 years) and gender (male vs. female), resulting in four strata: (1) males aged 18–40 years, (2) males aged 41–60 years, (3) females aged 18–40 years, and (4) females aged 41–60 years. Within each stratum, randomization sequences will be generated using permuted blocks to ensure balance until a total of 40 participants per group are enrolled (120 in total).

The randomization sequence will be generated by an independent research assistant who is not involved in the study, using GraphPad QuickCalcs, a validated web-based program for generating block randomization schemes. Allocation codes will be sealed in sequentially numbered opaque envelopes prepared by independent personnel. At enrolment, envelopes will be opened in sequence by study staff according to the order of patient visits, ensuring allocation concealment. Participants will be informed that they have an equal probability of assignment to each of the three groups.

This study will be conducted as a single-blind trial. Participants, outcome assessors, data collectors, and statisticians will remain blinded to group allocation, while acupuncturists delivering the interventions cannot be blinded due to the nature of the procedures. To maintain blinding integrity, acupuncturists will strictly follow a standardized intervention manual to minimize performance bias.

During treatment, participants will receive therapy in a closed room and will be required to wear blindfolds to prevent observation of laser irradiation. Communication among participants will be restricted, and scheduling will minimize cross-interaction. Researchers will not access unblinded data until data collection and statistical analysis are complete. Allocation concealment and restricted data access will further reduce the risk of bias, thereby strengthening the methodological rigor of the trial.

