SLA procedures. The sham condition used sham laser applied to the same acupoints as the LA group. Identical probes were secured with medical tape and positioned per the standardized manual, but the device delivered 0 mW output while maintaining the same indicators (lights/sounds) to preserve blinding. Session structure (per-point exposure time, total duration, number of sessions, and treatment sequence) matched the active protocol. Participants and outcome assessors were blinded; operators followed a standardized script. Regarding the validity of sham laser as a control procedure for laser acupuncture studies, in a study which evaluated the use of SLA as a control procedure by comparing verum laser with sham laser reported that treatment with verum laser was indistinguishable from sham laser and there was also no difference in the deqi-like sensations felt by study participants when comparing verum laser with sham laser. Then, the authors also analyzed the pooled findings of three RCTs that compared the use of sham laser with needle acupuncture and found that the credibility of sham laser was not different from that of needle acupuncture (39). Hence, sham laser can serve as valid placebo procedure in laser acupuncture studies.

Control group. Participants in the control arm will continue their stable antidepressant regimen without additional intervention. This group establishes a baseline comparator, enhancing the validity of between-group analyses.

Medication uses across groups. Antidepressant therapy must remain stable for ≥2 weeks before enrolment and throughout the trial. Rescue medication will be limited to oral eszopiclone 0.5 mg, to be taken as needed when insomnia persists for ≥3 consecutive nights. No other sedative–hypnotics (including benzodiazepines) will be permitted unless clinically necessary for safety; any exception requires documentation and approval by the principal investigator. All rescue-medication use will be logged (date, time, dose, indication) and reviewed regularly by the research team. If insomnia worsens alongside depressive symptoms, the participant will be withdrawn and referred for further management.

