### Statistical methods

All analyses will be conducted using statistical package for the social sciences (SPSS) version 28.0 (IBM Corp., Armonk, NY, USA) (51). Continuous variables will be summarized as mean ± standard deviation (SD) for normally distributed data, or as median (interquartile range, IQR) for non-normally distributed data. Categorical variables will be expressed as frequencies and percentages. A two-tailed p value < 0.05 will be considered statistically significant.

Primary outcomes. Changes in PSQI scores, sleep efficiency, total sleep time, and number of awakenings will be analyzed using a mixed-design ANOVA (52), with intervention group (LA, SLA, control) as the between-subject factor and time (baseline, post-treatment, follow-up) as the within-subject factor. Standardized mean differences will be calculated as effect sizes. Significant interactions will be followed by *post-hoc* pairwise comparisons. All primary analyses will follow the intention-to-treat (ITT) principle, with participants analyzed according to initial randomization regardless of adherence or withdrawal.

Secondary outcomes. ISI, HAMD-17, and biomarker levels (CORT, 5-HT) will be analyzed as continuous variables using mixed ANOVA across three time points. Actigraphy-derived sleep parameters will be analyzed similarly. Dropout rates due to AEs will be compared among groups using Pearson’s χ² test or Fisher’s exact test, as appropriate.

A subgroup analysis will be performed in which participants treated with LA will be subdivided into those on selective serotonin reuptake inhibitor (SSRI), serotonin noradrenaline reuptake inhibitor (SNRI) and other antidepressants and on low to moderate dose (less than optimal dose of antidepressant) and on high dose (above the optimal dose of antidepressant) using generalized estimated equation (GEE) where the dependent variable is dummy coded as 0 = without sleep quality disturbance (PSQI ≤ 5) and 1 = with sleep quality disturbance (PSQI > 5).

Sensitivity analysis. A per-protocol analysis will be conducted using the same statistical tests, excluding participants who fail to complete at least 5 of the 6 weekly intervention sessions. Findings will be compared with ITT results.

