Serum level of serotonin and cortisol is a window to what happen in the central nervous system (CNS). There is approximately 500 mL of cerebrospinal fluid (CSF) which is absorbed into the bloodstream from the CNS daily. Presence of psychiatric illness such as depression may lead to blood brain barrier dysfunction which allow increasing exchange of proteins between peripheral blood and CSF, which include hormone like cortisol and neurotransmitter such as serotonin. Hence, the serum cortisol and serotonin may represent what actually occurred in the brain (67).

This study is expected to contribute theoretically by integrating clinical outcomes with biomarker analyses to elucidate how LA may modulate both peripheral and central pathways involved in sleep and mood regulation (64, 67). Such findings may help establish a framework for incorporating non-invasive acupuncture techniques into holistic mental health care.

Several limitations should be acknowledged. First, recruitment from a single center may restrict the generalizability of results. Moreover, the effect size for estimation of sample size in this study was conservatively estimated and the sample size assumptions with reference to a previous RCT on effectiveness of LA for treatment of co morbid depression, anxiety and insomnia (50). Hence, this may also affects the generalizability of the study findings. Second, the relatively short follow-up period limits evaluation of long-term efficacy. Third, despite efforts at standardization, variability in acupuncturist training and resource allocation may introduce bias. Fourth, while standardized acupoint selection ensures reproducibility, it does not reflect individualized syndrome differentiation in TCM, which may be explored in future studies (68, 69). Fifth, although the sham laser procedure is operationally indistinguishable from the LA procedure, a pilot study for blinding assessment of the sham laser procedure is not performed. Hence, the risk of bias and compromise of blinding remains unresolved. Finally, the application of sham laser at identical acupoints as that of LA may induce non-specific physiological effects unrelated to laser output as the sham laser stimulate the acupoint area through pressure or contact which leads to activation of mechanoreceptors or nerve fibers that trigger neurological modulation, changes in blood flow or endorphin release (70, 71).

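### The 5-HT analysis names no log scale, baseline covariate or antidepressant class, which can cost power, and the Discussion reads a serum assay as evidence about the brain

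*Protocol article*

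**What the plan says.** Statistical methods, Secondary outcomes, sets the model: "ISI, HAMD-17, and biomarker levels (CORT, 5-HT) will be analyzed as continuous variables using mixed ANOVA across three time points". As for PSQI, the factors are group and time. The same section's provision for non-normal data concerns only how variables are summarised: "or as median (interquartile range, IQR) for non-normally distributed data". It attaches no consequence to the test.

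Inclusion criteria admit "patients on a stable dose of antidepressants (e.g., escitalopram, venlafaxine, or mirtazapine) for ≥2 weeks prior to enrolment", so more than one drug class is expected. Interventions (medication use across groups) adds: "Antidepressant therapy must remain stable for ≥2 weeks before enrolment and throughout the trial". Class is not a randomisation factor: "Stratification will be based on age (18–40 vs. 41–60 years) and gender (male vs. female".

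Class enters the analysis once, in a subgroup analysis where "participants treated with LA will be subdivided into those on selective serotonin reuptake inhibitor (SSRI), serotonin noradrenaline reuptake inhibitor (SNRI) and other antidepressants". There "the dependent variable is dummy coded as 0 = without sleep quality disturbance (PSQI ≤ 5) and 1 = with sleep quality disturbance (PSQI > 5"), so the outcome is binary PSQI and not 5-HT. Drug name and dose come from a daily medication diary (Secondary outcomes, Drug dose record).

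The biomarker is measured only in serum, by ELISA, at three time points. The Discussion nevertheless calls serum serotonin and cortisol a window onto the central nervous system and ends: "Hence, the serum cortisol and serotonin may represent what actually occurred in the brain". Its listed limitations mention neither the peripheral nature of the assay nor the background antidepressants.

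**The concern.** Change in biomarker levels is part of the hypothesis in the Introduction, and the mechanistic reading depends on it. Two things looked weak.

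First, concentrations are often right-skewed and treatment effects on them are often proportional. An ANOVA on untransformed values then gives most weight to patients with high levels, whose absolute changes and variances are both large. If patients on one drug class sit at a much lower 5-HT level, the same percentage effect is a small absolute change in them. The protocol itself names two of its three subgroup classes as serotonin reuptake inhibitors, yet uses class for sleep and not for serotonin. A real effect on 5-HT could be missed.

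Second, a positive result would be read through a Discussion that treats a blood assay as a readout of the brain.

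**Working it through.** **The plan's own figure.** There is none for 5-HT. The only sizing figure is 84 participants for the PSQI interaction. With λ = f²·N·m/(1−ρ), f = 0.158, N = 84, m = 3 and ρ = 0.5 (assumed; not stated), λ = 0.024964 × 84 × 3 / 0.5 = 12.58. On 4 and 162 degrees of freedom this gives power 0.810. The 84 reproduces, but says nothing about 5-HT.

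**Check 1: LA against SLA at one post-baseline visit.** All inputs are assumptions except 40 per arm (120 randomised 1:1:1): log SD 0.40 between and 0.30 within patients, a 25% increase under LA (ln 1.25 = 0.2231), and two thirds of patients on an SSRI or SNRI. Dropout is ignored. With two time points the group-by-time test is the t test on change.

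Closed form on the log scale:
- Total variance = 0.16 + 0.09 = 0.25; ρ = 0.16/0.25 = 0.64.
- Log change: variance 2 × 0.09 = 0.18; SE = √(0.18 × 2/40) = 0.0949; z = 2.352; power ≈ Φ(2.352 − 1.99) = 0.64.
- Log, baseline-adjusted: variance 0.25 × (1 − 0.64²) = 0.1476; SE = √(0.1476 × 2/40) = 0.0859; z = 2.597; power ≈ Φ(0.607) = 0.73 (0.72 by simulation).
- A ten-fold class difference left out of the baseline-adjusted model adds (2/3)(1/3)(ln 0.1)² = 1.178 to the between-patient variance. Then ρ = 1.338/1.428 = 0.937, the residual variance is 1.428 × (1 − 0.937²) ≈ 0.174, SE ≈ 0.0934 and power ≈ 0.66. A class term brings the variance back to 0.1476.

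Simulated power, by the 5-HT level of SSRI/SNRI patients relative to the others:

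| Level ratio | Raw change | Raw change + class | Log, baseline | Log, baseline + class |
|---|---|---|---|---|
| 1.0 | 0.60 | – | 0.72 | 0.72 |
| 0.5 | 0.55–0.56 | 0.54–0.55 | 0.70 | 0.72 |
| 0.3 | 0.47–0.48 | 0.48 | – | 0.72 |
| 0.1 | 0.32 | 0.32–0.33 | 0.66 | 0.71–0.72 |

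Log change stays at 0.64 for every ratio, because a fixed ratio between classes cancels in it. With no class difference, the log scale therefore gives about 4 points (0.60 to 0.64), baseline adjustment about 8 (0.64 to 0.72) and class none. At ten-fold, the log scale gives about 32 (0.32 to 0.64), baseline adjustment about 2 and class about 6.

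**Check 2: the planned three-group, three-time interaction.** Here 28 completers per arm were used (84/3), with class balanced across arms, 50–90% of patients on reuptake inhibitors, and a proportional LA effect sized for about 80% power on the log scale:

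| Log SD between/within | Log test | Raw, ratio 1 | Raw, 0.5 | Raw, 0.2 | Raw, 0.1 |
|---|---|---|---|---|---|
| 0.3/0.2 | 0.80–0.82 | 0.80 | 0.74–0.77 | 0.52–0.61 | 0.28–0.53 |
| 0.5/0.3 | 0.78–0.79 | 0.71–0.72 | 0.66–0.67 | 0.46–0.53 | 0.26–0.47 |
| 0.8/0.4 | 0.79–0.80 | 0.54–0.55 | 0.50–0.53 | 0.34–0.39 | 0.21–0.34 |

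Adding class by time to the raw model recovers 0 to 7 points; on the log scale it changes nothing. Type I error of the raw test is 0.02–0.05. With additive errors and an additive class shift of 0, −1 or −3 between-patient SDs, power is 0.56, 0.56 and 0.57, so pooling alone costs nothing.

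**Interpretation.** Nothing central is measured. The Discussion's bridge to the brain is an increased exchange of proteins said to include cortisol and serotonin; neither is a protein, so the argument does not carry as written.

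**The case against.** The strongest reply is that silence is not a choice. The article does not say that 5-HT is untransformed, and scale and covariates for a secondary biomarker may be set in an analysis plan that is not shown. That stands as far as it goes: an untransformed analysis is the natural reading of the text, not a stated fact. The article does, however, name the model and confine its non-normality rule to summaries, so the scale is worth fixing in writing.

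A reader might infer that pooling patients on different antidepressants biases the 5-HT comparison or is what costs power. The documents do not support this. Allocation is random, dosing is to stay stable, and a stable additive class difference cancels within patients. A class term on the raw scale recovers little or nothing.

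A reader might also infer that reuptake inhibitors are known to lower serum 5-HT several-fold. No passage says so, and the class ratios used here are only an assumed range. With mild skew and similar classes the raw test loses nothing (0.80 against 0.80).

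On the brain reading, the concluding sentence says only that serum levels may represent central events, it cites a source, and the Introduction speaks of exploring effects on serum levels. No analysis depends on it. That lowers the weight of the point, but the window statement is unhedged and the limitations do not qualify it.

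**Conclusion.** The concern holds in a limited form. The group-by-time ANOVA for 5-HT is valid but may be inefficient. The loss ranges from nothing to large, depending on skewness, on whether the LA effect is proportional and on how far classes differ, none of which the protocol gives. In the illustrative LA–SLA case it is 12 points with no class difference (0.60 against 0.72) and about 40 points at a ten-fold difference (0.32 against about 0.72). Both figures ignore the roughly 30% dropout that the protocol expects. Scale and baseline adjustment account for most of the gain, and class for 0 to 7 points. Separately, a serum-only assay cannot support a conclusion about the brain. Severity is low: 5-HT is secondary and the PSQI analysis is untouched.

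**What to change.** In Statistical methods, Secondary outcomes, specify that post-baseline log 5-HT is analysed with baseline log 5-HT as a covariate. Add antidepressant class at enrolment (SSRI/SNRI against other) as a further covariate or as a sensitivity analysis, and report the result as LA-to-SLA ratios with confidence intervals.

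In the Discussion, state that serum 5-HT and cortisol are peripheral measures taken under ongoing antidepressant treatment, and limit the mechanistic conclusion to peripheral levels.

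The cost is a few sentences, settled before unblinding. No new data are needed, since baseline samples and drug names are already collected. The downsides are that results are stated as ratios and the mechanistic claim becomes narrower.

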### Withdrawal criteria

Withdrawal criteria are as follows: (1) emergence of suicidal tendencies during the study; (2) occurrence of SAEs; and (3) worsening of insomnia that aggravates depressive symptoms.

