### Sample size calculation

Sample size estimation was performed using G*Power version 3.1.9.2 (Heinrich Heine University, Düsseldorf, Germany) (49). The calculation was based on a repeated-measures, between–within interaction analysis of variance (ANOVA) with the changes in PSQI across time as the primary outcome. An effect size of f = 0.158 was adopted from a RCT investigating LA in patients with co morbid insomnia, depression and anxiety (50). This effect size was chosen as a conservative estimate, reflecting clinically meaningful but mild improvements in sleep quality. Parameters were set at a two-tailed significance level (α) of 0.05, statistical power (1–β) of 0.80, number of groups = 3 and number of measurements = 3. Under these conditions, the minimum required sample size was calculated to be 84 participants across three arms. To account for an anticipated dropout or attrition rate of approximately 30%, the final adjusted sample size was set at 108 participants, with 36 subjects per group (LA, SLA, and control). This sample size is expected to provide sufficient power to detect between-group differences and to remain robust against missing data or attrition.

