Missing data. If <5% of data are missing, they will be ignored under the assumption of missing completely at random. When missingness is between 5% and 40%, multiple imputation using chained equations will be applied (Stata 15.0, StataCorp, College Station, TX, USA) (53). If >40% of data are missing or suspected to be non-random, available data will be analyzed with explicit acknowledgment of this limitation.

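### At the anticipated 30% attrition, two missing-data branches can both apply with no precedence, and one of them drops imputation and turns the primary mixed-design ANOVA into a completer analysis

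*Protocol article*

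**What the plan says.** All of this is in the Protocol article.

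- **Missing data, first branch:** "If <5% of data are missing, they will be ignored under the assumption of missing completely at random".
- **Second branch:** "When missingness is between 5% and 40%, multiple imputation using chained equations will be applied".
- **Third branch:** "If >40% of data are missing or suspected to be non-random, available data will be analyzed with explicit acknowledgment of this limitation".
- **Primary analysis (Statistical methods):** PSQI "will be analyzed using a mixed-design ANOVA (52), with intervention group (LA, SLA, control) as the between-subject factor". The repeated factor is the visit, with three levels: t0, t1 and t2.
- **Analysis population (Statistical methods):** "All primary analyses will follow the intention-to-treat (ITT) principle, with participants analyzed according to initial randomization regardless of adherence or withdrawal".
- **Expected loss (Sample size calculation):** attrition of approximately 30%.
- **Withdrawal criteria:** one of the three is "worsening of insomnia that aggravates depressive symptoms". The paragraph on medication use across groups repeats withdrawal on this ground.

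The only sensitivity analysis that the article names is per-protocol.

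**The concern.** The third branch has two triggers joined by an *or*: more than 40% missing, or suspected non-random missingness. The second trigger has no percentage attached, so it can be met inside the 5–40% band. The plan then gives two instructions for the same data, to impute or to analyse what is available. It does not say which prevails or what would count as suspicion.

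The two instructions lead to different analyses. An analysis restricted to complete records is safest when missingness is unrelated to outcome. The third branch selects it when that assumption is least credible, and acknowledging a limitation does not correct the bias. The withdrawal criterion is tied to what the PSQI measures, so outcome-related loss is foreseeable. At stake is who enters the primary comparison, and whether that is decided before or after the data are seen.

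**Working it through.** **1. Which branch applies at the anticipated attrition?**
If 30% of 120 patients are lost, 0.30 × 120 = 36 have incomplete data. Counted by patients, that is 30% missing. Counted by PSQI values (120 × 3 = 360), it is 36/360 = 10% if only t2 is lost, and 72/360 = 20% if t1 and t2 are both lost. Each figure lies in the 5–40% band, so on percentage alone the plan imputes. If missingness is also suspected to be non-random, the third branch applies as well.

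**2. What does the available-data branch do?**
A classical mixed-design ANOVA needs a value at every level of the within-subject factor. This is a general property of the method; the article does not state it. A participant with PSQI at t0 and t1 but not t2 is dropped, and the observed week-6 score is lost. Set beside the promise to analyse participants "with participants analyzed according to initial randomization regardless of adherence or withdrawal", that is a conflict. The second branch has no such conflict, because imputed data sets give the ANOVA all three visits for everyone.

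**3. Power, conditional on the available-data branch**
Inputs from Sample size calculation: f = 0.158, α = 0.05, k = 3 groups, m = 3 measurements, target power 0.80, stated N = 84. Assumed because not stated: correlation ρ = 0.5 among measurements, and sphericity.

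λ = N·f²·m/(1 − ρ), df1 = (k − 1)(m − 1) = 4, df2 = (N − k)(m − 1).

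- *The plan's own figure:* the smallest N with power 0.80 is 83, or 84 in three equal arms. At N = 84, λ = 84 × 0.024964 × 3/0.5 = 12.58, df2 = 162, power 0.810. The stated 84 is reproduced.
- *Dependence on ρ:* ρ = 0, 0.3, 0.6 and 0.7 give N = 162, 114, 67 and 51, so ρ = 0.5 is the value among these that fits the plan.

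The article gives 120 randomised (Study design) and 108 (Sample size calculation). That is a separate matter, so both are shown.

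| Randomised | Power with no loss | Completers at 30% loss | Power, completers only |
|---|---|---|---|
| 120 | 0.938 | 0.70 × 120 = 84 | 0.810 |
| 108 | 0.908 | 0.70 × 108 = 75.6, taken as 75 | 0.757 |

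The no-loss column is a ceiling. Imputation would not recover all of it.

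**4. Direction of bias (illustration only)**
The first two rows assume PSQI SD 3, correlation 0.5, means 13, 9, 9 (LA) and 13, 11, 11 (SLA), and 30% overall dropout at t2 that is more likely with a worse score (about 23% in LA and 37% in SLA). The third row is a two-arm, baseline-to-post set-up in SD units with correlation 0.5. There, 80% of patients who worsen are lost plus 10% at random, giving about 38% loss in SLA and 21% in LA.

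| Loss driven by | True LA–SLA difference | Completers | Missing-at-random analysis |
|---|---|---|---|
| Observed week-6 score | 1.99 points | 1.82 | 2.00 |
| Unobserved follow-up score | 2.00 points | 1.65 | 1.74 |
| Worsening on the unobserved score | 0.71 SD | 0.49 | 0.53 |

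Completers are the more biased choice in every row, and the bias is towards no difference. When observed scores explain the loss, a missing-at-random analysis removes the bias. When they do not, it removes only part.

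**The case against.** The strongest reply is that the plan already imputes at the attrition it expects. That stands. A reader might infer that 30% attrition by itself makes the primary analysis a completer analysis, or that 36 patients will be lost from it. The documents do not support this: 30% lies in the imputation band, and the loss occurs only if the non-random or above-40% trigger is invoked (and, trivially, below 5%).

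A reader might also infer that the available-data branch is the likely one. The article does not say what share of the 30% would be withdrawals for worsening, and outcome-related loss that observed scores explain can be missing at random. The branch is foreseeable; likely is more than can be shown.

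Statisticians are to remain blinded, which limits steering of the choice by group results. It does not supply a criterion or change what the branch does.

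Multiple imputation followed by ANOVA is a legitimate route, so the choice of ANOVA is not itself the defect. A sensitivity analysis for non-random missingness may sit in an analysis plan not shown, so its absence from the article is not the finding. The finding is the rule as stated.

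**Conclusion.** The concern holds in conditional form. The rule as written allows two incompatible analyses at the anticipated attrition, gives no precedence, and sends suspected non-random data to the method with the stronger missingness assumption. If that branch is taken at 30% loss, 36 of 120 randomised patients leave the primary ANOVA and the intention-to-treat commitment is not met. Power is then about 0.81 (84 of 120) or 0.76 (75 of 108).

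These figures assume a classical ANOVA with casewise deletion, a correlation of 0.5, sphericity, and no later PSQI from patients who are lost.

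No bias figure should be attached to this trial. The simulated effects and dropout mechanisms are not in the documents. Losing treatment failures might suggest an inflated LA effect, but in the scenarios tried the difference shrank. Nor would a likelihood-based mixed model alone cure the problem: the last two rows of the simulation table show that bias remains when loss depends on unobserved scores.

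**What to change.** 1. Delete suspected non-randomness as a reason to abandon imputation.
2. Replace the percentage-driven rule by one primary approach at every level of missingness that keeps all randomised patients and all observed PSQI scores. Either multiple imputation throughout or a likelihood-based linear mixed model with group, visit and group × visit would serve.
3. Where non-random missingness is suspected, add a delta-adjusted or reference-based multiple-imputation sensitivity analysis in place of the available-data analysis, because neither primary option alone removes non-random bias.

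The cost is revised wording in the statistical section and a little more analysis work. No new data are needed. It should be settled before outcome data are seen, and preferably before recruitment, which is scheduled from December 2025.
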